### Randomization

The study will employ an electronic data capture (EDC) system for case enrolment and random assignment of treatment groups using the minimization method. Blinding of the study is conducted based on an allocation chart prepared by the study drug allocation manager, with only the drug number notified by the EDC system. Stratification factors include age ≥ 75 years at enrolment, highly invasive surgery scheduled for ≥6 hours, benzodiazepine and non-benzodiazepine use and the site of enrolment.

### Treatment methods

A flowchart of the study procedure is shown in Fig. 1. The study schedule is shown in Table 1. The test drug comprises Swedish orange capsules filled with ramelteon 8 mg formulation and an identical control capsule containing a lactose tablet of the same specification (same size and weight but ramelteon-free). One capsule of the study drug (test or control) will be administered orally or via a nasogastric tube once daily before bedtime during the medication period (double-blind). As a co-intervention, a combined intervention for the prevention of delirium will be implemented in all patients, according to the National Institute for Health and Clinical Excellence Guideline ‘Delirium: prevention, diagnosis and management’, e.g. patients are provided clinically appropriate care if they have cognitive impairment, disorientation, dehydration, constipation, hypoxia, infection, immobility, pain, benzodiazepine and/or anti-benzodiazepine prescription, poor nutrition, sensory impairment and insomnia (12).

**Table 1 TB1:** Study schedule

[figure not shown]

Note 1: If the patient comes to the hospital after consent has been obtained and before preoperative admission, consent will not be obtained again.

Note 2: If the duration of administration can be secured, protocol treatment will start earlier during a period denoted by triangles.

Note 3: The Nursing Delirium Screening Scale will only be administered at the National Cancer Center Hospital.

Note 4: Details of the blood tests are as follows:

1. Total bilirubin, aspartate transaminase (AST) and alanine transaminase (ALT) at the date of registration are adopted from blood test results performed in clinical practice within 8 weeks retrospectively from the date of registration.

2. Adopt clinically performed blood test results for total bilirubin, AST, ALT and C-reactive protein on the first postoperative day.

Note 5: Adverse effects such as somnolence, floating dizziness, malaise, headache, constipation, nausea and urticaria should be investigated.

ALT, alanine transaminase; AST, aspartate transaminase; DRS, Delirium Rating Scale; DSM, Diagnostic and Statistical Manual of Mental Disorders; ESAS-r; Edmonton Symptom Assessment System Revised Japanese Version; Nu-DESC, Nursing Delirium Screening Scale

### Follow-up

The planned follow-up period is 12 weeks.

### Sample size

The proportion of delirium in patients aged ≥75 years is assumed to be 24% in the ramelteon group and 36% in the control group. With a two-sided alpha error of 0.05 and power of 0.90, the required sample size is calculated at 610 patients. We therefore plan to enrol 678 patients aged ≥75 years (339 per group) to allow for a 10% dropout. The proportion of delirium in patients aged ≥65 years is assumed to be 22% in the ramelteon group and 33% in the control group. With a two-sided alpha error of 0.05 and power of 0.90, the required sample size is calculated at 690 patients. Therefore, 766 patients (383 per group) would be required to allow for 10% dropout. We thus plan to enrol 88 patients aged 65–74 years in addition to the 678 patients aged ≥75 years. The study will continue to enrol both age groups until the planned enrolment of 88 patients in the 65- to 74-year-old group and 678 patients in the ≥75-year-old group is met.

### Statistical analysis

We will calculate point estimates and 95% confidence intervals for the proportion of patients in each group aged ≥75 years with delirium in the 5 days after surgery as diagnosed by a psycho-oncologist using the DSM-5 and compare groups using the Cochran–Mantel–Haenszel test adjusted for stratification factors. The significance level is set at 5% (two-sided). If a statistically significant between-group difference is found for age ≥ 75, a similar comparison will be made for those aged ≥65 without adjustment for statistical multiplicity. If the superiority of the ramelteon group is confirmed, ramelteon treatment will be considered a useful prophylaxis.

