### Exclusion criteria

Patients in whom any one of the following applies are excluded:

Patients with a Diagnostic and Statistical Manual of Mental Disorders-5 (DSM-5) (27) diagnosis of delirium at the time of enrolment.Patients with a history of allergy to ramelteon.Patients with severe hepatic dysfunction defined as aspartate transaminase >90 U/L, alanine transaminase (ALT) >126 U/L (men), ALT >69 U/L (women) and total bilirubin >2.25 mg/dl.Patients who were participating in a clinical trial or clinical study with a new drug within 4 weeks of enrolment, including the date of enrolment (patients who have completed protocol treatment and are in the observation period are excluded).Patients taking ramelteon within 2 weeks of registration, including the date of registration, and fluvoxamine, with which there is a known interaction (28).Patients who have taken an orexin receptor antagonist (suvorexant or lemborexant) within 2 weeks of enrolment, including the date of enrolment.Patients with a history of epilepsy, Parkinson’s disease or dementia with Lewy bodies.Patients with a history of lactose intolerance.Patients whose planned resection includes central nervous system and intracranial areas.Patients with drug or alcohol use disorders within 5 years of enrolment, including the date of enrolment; patients who consume an average of 60 g of alcohol daily (e.g. 3 g of sake, three medium bottles of beer and five glasses of wine) or more; and patients with alcohol-related diseases (e.g. alcoholic liver disease).Patients who have previously participated in this study.Patients with moderate or severe dementia (Mini-Mental State Examination Japanese Version score < 21) (29).Patients with severe visual, hearing or reading impairments.Patients deemed unsuitable by the principal investigator or sub-investigator.

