### Endpoints

The primary efficacy endpoint is the proportion of patients aged ≥75 years with delirium in the first 5 days after surgery as diagnosed by a trained psycho-oncologist using the DSM-5 (27). The secondary efficacy endpoints are as follows:

Delirium in the first 5 days after surgery as diagnosed by a psycho-oncologist using the DSM-5. This will be verified only if a significant effect is found in the primary analysis population. If a significant effect is not found in the primary analysis population, this will be analysed as an exploratory endpoint only.The remaining secondary endpoints will be investigated in all age groups and using stratified analyses (stratified into patients aged ≥75 years).The proportion of delirium in the first 5 days after surgery as diagnosed by psycho-oncologists using the DSM-5 (excluding delirium within 2 hours after surgery).Proportion of delirium in the first 5 days after surgery as assessed by nurses using the Nursing Delirium Screening Scale (Nu-DESC) (30).Delirium severity at 5 days after surgery as assessed using the Japanese version of the Delirium Rating Scale (DRS)-R-98 (31,32) and Nu-DESC.The proportion of cases of severe delirium in the first 5 days after surgery diagnosed by DSM-5 and DRS-R-98.Days from diagnosis to resolution of delirium according to DSM-5.Direct medical costs from post-surgery to discharge.Postoperative hospital stay.The proportion of antipsychotic use in the first 5 days after surgery.The proportion of patients stopping or withdrawing from benzodiazepines and non-benzodiazepines on the day prior to surgery.The proportion of falls, self-removal of any tubes including drip infusions and self-extubation and physical restraint within 5 days of surgery.Serum C-reactive protein level on the morning of the first postoperative day.Percentage of postoperative complications [Clavien–Dindo (CD) category grade ≥ 2] in the first 5 days after surgery.The proportion of postoperative complications (CD grade ≥ 2) within 90 days of surgery.Survival within 30 days after surgery.Survival up to 90 days after surgery.Recurrence-free survival within 90 days after surgery.Patient satisfaction with study participation and subjective symptoms on postoperative day 5 (Edmonton Symptom Rating System, modified Japanese version) (33).Percentage of patients who cannot be discharged home.Proportion of delirium in the first 5 days after surgery diagnosed by a psycho-oncologist using the DSM-5, with a Pittsburgh Sleep Quality Index (PSQI) (34) of ≥6 and a PSQI of ≤5 at enrolment.

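### The primary CMH test in patients aged 75 or over makes no adjustment for age and leaves the entry MMSE score unused; pre-specifying both would probably add a little precision

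*Protocol article*

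**What the plan says.** The Endpoints section restricts the primary question by age: "The primary efficacy endpoint is the proportion of patients aged ≥75 years with delirium in the first 5 days after surgery". For that population the Statistical analysis section gives a proportion with a 95% confidence interval in each arm, and for the comparison it will "compare groups using the Cochran–Mantel–Haenszel test adjusted for stratification factors".

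The Randomization section lists those factors: "Stratification factors include age ≥ 75 years at enrolment", then surgery scheduled to last 6 hours or more, use of benzodiazepines or non-benzodiazepines, and enrolment site. Three hospitals are named under Study setting and patients.

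Two other baseline measures are needed before a patient can enter. The eligibility criteria require age at registration. The exclusion criteria require a cognitive score: "Patients with moderate or severe dementia (Mini-Mental State Examination Japanese Version score < 21". The Statistical analysis section names neither age in years nor the MMSE score as a covariate.

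**The concern.** Adjusting for the stratification factors sounds as if it includes age. In the primary population it does not: every patient is in the same age category, so that factor contributes nothing to the CMH strata.

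The plan's own figures treat age as prognostic. The assumed control rate is 36% at 75 and over but 33% at 65 and over. Cognition is likely to matter too, since the Treatment methods section lists cognitive impairment among the problems that the co-intervention addresses.

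If either variable predicts delirium within the primary population, adjusting for it reduces the variance of the treatment effect without more patients. What is at stake is some precision and power. Validity is not at stake.

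**Working it through.** **1. Reproduce the planned sample size.** Inputs from the Sample size section: 24% v 36%, two-sided alpha 0.05, power 0.90. With pooled variance and no continuity correction, and mean rate 0.30:

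n per arm = [1.960·√(2·0.30·0.70) + 1.2816·√(0.24·0.76 + 0.36·0.64)]² / 0.12²
= [1.960·0.6481 + 1.2816·0.6425]² / 0.0144 = 4.383 / 0.0144 = 304.4, so 305.

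The total is 610, as stated, and 610/0.9 = 678 with dropout, also as stated. Power at 305 per arm is 0.901. No covariates are needed to reach it.

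**2. What the CMH test adjusts for.** Four factors are listed, and age ≥75 is constant in the primary population. Surgery (2 levels) × drug use (2) × site (3) leaves 12 strata, none of them defined by age.

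**3. Does the plan treat age as prognostic?** Suppose the 33% control rate at 65 and over describes the planned mix of 678 older and 88 younger patients (an assumption). The implied control rate at 65–74 is then

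(766·0.33 − 678·0.36)/88 = (252.78 − 244.08)/88 = 8.70/88 ≈ 10%.

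That is far below 36%. It shows an age gradient across the cut at 75; the gradient above 75 is not given.

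**4. Size of the gain, by simulation.** Settings: 610 patients, 36% v 24%, and a 12-stratum CMH test compared with a logistic model that adds age and MMSE as standardised covariates (1,500 trials per row). Assumptions not in the article: odds ratios per SD as in the table; long surgery in 30% of patients (odds ratio 1.8); drug use in 20% (odds ratio 1.5); no site effect; simple balanced allocation in place of minimization. The variance ratio is for the standardised risk difference, with the two covariates relative to adjustment for surgery and drug use only.

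| Odds ratio per SD, age/MMSE | Variance ratio | CMH power | Logistic power | Gap (points) | Gap less 1.4 |
|---|---|---|---|---|---|
| 1.0/1.0 | 1.00 | 90.6% | 92.0% | 1.4 | 0 |
| 1.2/1.3 | 0.99 | 88.3% | 89.8% | 1.5 | 0.1 |
| 1.4/1.6 | 0.96 | 89.4% | 91.7% | 2.3 | 0.9 |
| 1.6/2.0 | 0.89 | 90.1% | 93.9% | 3.8 | 2.4 |

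The 1.4-point gap in the first row arises with covariates that predict nothing. It reflects the choice of test (the logistic model here left out site), so the last column is the part due to the covariates.

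A second simulation against the same 12-stratum CMH test, over the same range of odds ratios, gave variance ratios of 1.00 to 0.88 and power gains of about 0 to 4 points. Type I error was kept (0.044).

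**5. Cross-check by formula.** Take the most favourable ratio, 0.88. The effective size is 305/0.88 = 346.6 per arm, and

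power = Φ[(0.12·√346.6 − 1.960·0.6481)/0.6425] = Φ(1.50) = 0.933,

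which is about 3 points above 0.901 and within the simulated range. For the risk difference, the 95% CI half-width at the design rates is 1.96·√[(0.1824 + 0.2304)/305] = 7.2 points. It would become 7.2·√0.88 = 6.8 points. The same precision would need 610·0.88 = 537 patients.

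**The case against.** The strongest reply is that nothing here is wrong. A CMH test on the allocation factors is valid, simple and fixed in advance; randomization balances age and MMSE in expectation; and leaving them out neither biases the test nor inflates type I error. All of that stands.

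It is also fair that the gain is assumed. The article gives no association between delirium and age or MMSE among patients aged 75 or over. Excluding scores below 21 and ages below 75 narrows the spread of both covariates, so the upper end of the range may not be reached. At odds ratios of 1.2/1.3 the gain is close to nothing. The comparison must also be made against the planned stratified test, because an unadjusted comparator is not the plan.

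Two practical limits stand as well. That the MMSE score is stored as data is inferred from the exclusion rule, since the schedule table is not shown. And a model needs decisions that a CMH test does not.

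A reader might go further and infer from "We will calculate point estimates and 95% confidence intervals for the proportion of patients in each group aged ≥75 years with delirium" that no between-group effect with a confidence interval will be reported. The article does not support that. It names no such measure, but it does not say that only a p-value will be given, and the measure that accompanies a CMH test is a detail that a condensed article commonly leaves to the analysis plan.

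**Conclusion.** The point holds as a low-severity improvement. The article fixes an adjustment set that contains no age information in the primary population and does not use a cognitive score that must be obtained before entry. Under the assumed odds ratios per SD (age/MMSE from 1.0/1.0 to 1.6/2.0), adding the two covariates lowers variance by about 0 to 12% and raises power by about 0 to 4 points over the planned CMH test. Part of that power gain can come from the change of test and not from the covariates. In these simulations the covariates brought no material loss of precision.

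A reader might take this to mean that the primary test is invalid or the trial underpowered. Neither follows: the sample size of 610 reproduces exactly and gives the stated 90% power as planned.

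**What to change.** Before unblinding, pre-specify the primary effect as a standardised risk difference with 95% CI and test. Take it from a logistic model with treatment, site, scheduled surgery of 6 hours or more, benzodiazepine or non-benzodiazepine use, age in years and, if the score is recorded as data, baseline MMSE. Keep the CMH test on the stratification factors as a supportive analysis.

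The cost is wording in the protocol and analysis plan and a few lines of code. Three things must be written down in advance: how age and MMSE enter the model, how a missing MMSE score is handled, and how the variance is estimated given allocation by minimization. No new data are expected. If the MMSE score proves not to be stored, age in years can be added alone.

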### Interim analysis and monitoring

Because of the small differences between groups to be detected, no interim analysis will be performed.

